**Fig. 1 Fig1:**
[figure not shown]
Overview of modules and procedures as part of the CCSchool stepped-care-model

### Control group

The control group follows a waiting list design. Recruited children and adolescents, who attend school in a control group district, will receive treatment as usual (TAU) for 12 months. Level of functioning (C-GAF), level of impairment (CIS), quality of life (KIND-L) and days of school absenteeism will be recorded at recruitment (T1), as well as after six (T2) and 12 months (T3). After 12 months the parents and child/adolescent will be screened again for eligibility and – if still eligible - offered to enter the intervention part of the study and participate in module A as well as B and C if necessary. After an additional 6 months or after completion of module C the last assessment (T4) will take place.

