## Methods/design

CCSchool comprises the following three modules as part of a stepped-care model:Module A: standardized diagnostic procedure,Module B: School-based assessment followed by a first intervention (therapeutic assessment)Module C: School-based treatment.

There are two kinds of therapists working on one case: Responsible Therapists (RT) and CCSchool-Therapists (CCST).

The RT manages the case and decides which patients enter module A and may receive the treatment of the modules B and C in addition to module A. The role of the RT can be assumed by physicians, psychologists and other mental health professionals specializing in child and adolescent psychiatry/psychotherapy or paediatrics.

Eligible as CCSchool-Therapist (CCST) are occupational therapists, psychologists in training, social workers, nurses and other health professionals. The CCST will conduct the school-based assessment and the school-based interventions (modules B and C).

All of the participating therapists (RTs and CCSTs) have to complete an e-learning programme before being eligible to recruit or work with patients in CCSchool.

Students suspected of mental health problems associated with school problems, will undergo a screening for CCSchool. Students can be referred to the screening procedure either by (a) parents, (b) a paediatrician/child and adolescent psychiatrist/GP.

Inclusion criteria area psychiatric diagnosis andschool problems (academic or social) pointed out by the teacher or parents or high scores on the school-items of the Columbia Impairment Scale (CIS) filled-in by parents and/or students anda psychosocial functioning level on the Children Global Assessment of Functioning Scale (C-GAF) equal or below 70.

Exclusion criteria are: primary diagnosis of substance abuse or an issue of child protection that has to be addressed first.

Once found eligible for CCSchool, the parents and the child or adolescent will be informed about the study, and, if they are interested in participation, parents and child/adolescent will be asked to sign an informed consent form.

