### Evaluation and study analyses

An external independent research institute (IGES Institute GmbH) will evaluate the achievement of the endpoints in CCSchool. The evaluation will use primarily data collected and assessed during the study on level of functioning, level of impairment, absenteeism and quality of life as well as data from documentation and process evaluation. In addition, claims data from the statutory health insurances will be analysed.

The study uses a cluster-randomized design with a waiting-list control group. Participating districts will be randomly assigned to an intervention and a control group. Children and adolescents, who are eligible for participation, will be allocated in the control versus intervention group depending on the location (district) of their school to avoid situations where there are intervention and control participants in the same school/class. The evaluation will compare the resulting intervention and control group participants on all outcome variables. In addition, claims data on the CCSchool participants as well as on children and adolescents with the same inclusion diagnoses (a) living in districts not included in the study and (b) living in the CCSchool districts before CCSchool has started (historical comparisons) will be analysed. These external control participants are matched to the intervention participants by propensity score matching. The claims data allows validating the self-reported data on hospitalization rates and analysing potential effects on health care costs.

The statistical analyses of the comparisons between randomized control group, external control group and intervention group will use a multilevel framework taking the cluster randomisation into account. Longitudinal regression analyses of changes in hospitalization rates, quality of life, symptoms and absenteeism are conducted using mixed models adjusting for potential confounders (e.g., age, gender, regional characteristics). This approach is feasible to estimate within-person changes over time as well as group differences in within-change over time. For process evaluation, cross-sectional group comparisons will be analysed with regression models without repeated measures and descriptive statistics. All effects will be tested with a significance level of *p* ≤ .05.

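### Child-by-child crossover in control districts can bring modules B and C into schools where later-recruited controls are still in their treatment-as-usual year; school start dates should be recorded and a sensitivity analysis pre-specified

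*Protocol article*

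**What the plan says.** Evaluation and study analyses states that eligible children "will be allocated in the control versus intervention group depending on the location (district) of their school", and gives the reason: "to avoid situations where there are intervention and control participants in the same school/class".

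Control group states that "The control group follows a waiting list design". It then sets the timing per child:

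- "Recruited children and adolescents, who attend school in a control group district, will receive treatment as usual (TAU) for 12 months".
- Outcomes are "recorded at recruitment (T1), as well as after six (T2) and 12 months (T3"), so the clock starts at the child's own recruitment.
- "After 12 months the parents and child/adolescent will be screened again for eligibility and", where still eligible, "offered to enter the intervention part of the study and participate in module A as well as B and C if necessary".

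Methods/design describes entry by individual referral: "Students can be referred to the screening procedure either by (a) parents", or by a paediatrician, child and adolescent psychiatrist or GP.

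Under Module B, the CCSchool therapist observes the child in class and at recess and interviews the class-teacher, who may also join the feedback meeting. Under Module C, teacher psychoeducation is one of several possible interventions.

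**The concern.** District allocation protects the contrast only while the intervention stays out of control-district schools. The per-child clock lets it in before all controls there have finished their usual-care year. A later-recruited control may then share a school, and perhaps a teacher, with a crossed-over child who is receiving modules B or C. The Module C section says that the question is whether applying standard methods in school makes a difference, so in-school delivery is the very thing being contrasted.

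This touches the randomised 12-month comparison itself, not only follow-up after month 12. If recruitment lasts up to 12 months, the exposed time always falls at the end of the later child's wait, just before the month-12 assessment. Exposure also rises with recruitment date, so it is entangled with calendar time. If nobody records when in-school work began in each control-district school, a null result could not be separated from dilution.

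**Working it through.** **Timing.** A control child recruited at month *t* waits over [*t*, *t* + 12]. A schoolmate recruited at *s* can cross over from *s* + 12. With a lag of *L* months from re-screening to module B, in-school work starts at *s* + 12 + *L*. This falls before the later child's wait ends whenever *s* + *L* < *t*. With no lag, any earlier-recruited schoolmate who reaches module B creates some overlap. Only simultaneous recruitment within a school, or one control child per school, rules it out.

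**Inputs from the article.**
- About 90 children per district (Methods/design).
- Share reaching module B: 428/901 = 47.5% (Abstract).
- Wait of 12 months (Control group).

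**Assumptions, because the article gives no figure.**
- Even recruitment over *A* = 6, 12 or 24 months.
- *S* = 20, 40 or 80 recruiting schools per district, with children spread at random.
- *L* = 0 or 2 months.
- Every control child re-qualifies and accepts, which overstates exposure.

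**District-level upper bound.** Suppose the first control in a district crosses over at month 12 and the whole district then counts as exposed. A child recruited at *t* has min(*t*, 12) exposed months. The mean over *t*, divided by 12, is:
- *A* = 6: 3/12 = 25%.
- *A* = 12: 6/12 = 50%.
- *A* = 24: (72 + 144)/24 = 9, and 9/12 = 75%.

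**School level, the unit the stated aim refers to.** Let μ = 89 × 0.475/*S* be the expected number of other children in the same school who reach module B. For *A* ≤ 12 and *L* = 0, the mean exposed time in months is

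*A* × [1/2 − 1/μ + (1 − e^(−μ))/μ²].

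For *S* = 40, μ = 1.057. With *A* = 12 this is 12 × (0.500 − 0.946 + 0.584) = 1.66 months, and 1.66/12 = 14%.

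With a lag, replace *A* by *A* − *L* and μ by μ(*A* − *L*)/*A*, and multiply by (*A* − *L*)/*A*. For *A* = 24, exposure is capped at 12 months and the mean was computed numerically.

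Share of control waiting time in a school with module B already active (*L* = 0, with *L* = 2 in brackets):

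| Recruitment | 20 schools | 40 schools | 80 schools |
|---|---|---|---|
| 6 months | 11% (4%) | 7% (2%) | 4% (1%) |
| 12 months | 22% (14%) | 14% (8%) | 8% (5%) |
| 24 months | 38% (32%) | 24% (19%) | 13% (11%) |

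**Children with any exposed time.** With no lag this is 1 − (1 − e^(−μ))/μ: about 58% at 20 schools, 38% at 40 and 22% at 80. It does not depend on recruitment length, which drives the duration of exposure instead.

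**The case against.** The strongest counter-argument has five parts.

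- **The article is condensed.** Enrolment windows or a separation rule may stand in the full protocol. That is possible and would settle the matter. The point does not rest on that silence, though: the article itself states both the per-child clock and the aim of keeping the groups apart, and as stated the first works against the second.
- **A waiting list always brings treatment into control districts.** True, and the waiting list is not the issue. What matters is that treatment can arrive before other controls in the same school have finished.
- **The spill-over route is modest.** This stands. In module B the teacher fills in a form, is interviewed and may attend one meeting. Teacher psychoeducation is optional within module C, which the Abstract expects for 103 of 901 children (11%). Counting module C alone, with 40 schools and an assumed 3-month lag, exposed time is about 2% for 12 months of recruitment and 5% for 24.
- **Responsible therapists are not a crossover-specific route.** This also stands. All participating therapists must complete the e-learning before they recruit, so those recruiting controls are already trained.
- **Closing active control-district schools to further recruitment would be worse.** It would apply to one arm only, after randomisation, and so risks differential selection. It would also leave enrolled controls exposed. It is not recommended here.

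A reader might infer that 25–75% of control time is contaminated. Those figures describe a whole district after its first crossover, whereas the stated aim concerns schools and classes. A reader might also infer that the 12-month comparison is shown to be biased toward no effect. The documents give no evidence that one child's in-school work changes another child's admissions.

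**Conclusion.** The point holds as a design inconsistency of moderate and uncertain size. As written, crossover on individual clocks can place active module B or C work in a control-district school during other controls' usual-care year, which district allocation was meant to avoid.

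Across the assumed ranges, exposed control time is about 1–11%, 5–22% and 11–38% for 6, 12 and 24 months of recruitment. These figures depend on assumed recruitment length, number of schools, lag and full uptake after re-screening, none of which the article gives. They measure time in an exposed school, not loss of effect. Dilution of the 12-month contrast is the plausible direction; its amount, especially for inpatient admissions, is unknown. The finding does not invalidate the randomised comparison. It justifies a cheap safeguard.

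**What to change.** Leave the 12-month offer and the recruitment rules as they are.

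1. Record, for each control-district school, the date on which module B first starts there.
2. Pre-specify a sensitivity analysis of the 12-month comparison, adjusted for recruitment date:
   - **Hospitalisation:** censor control follow-up in a school at that date.
   - **C-GAF, CIS, KINDL and absenteeism:** either set aside control assessments made after that date, or add a time-varying indicator of school exposure to the planned mixed model. The indicator keeps the month-12 values, which matters because these outcomes are scheduled only at 0, 6 and 12 months of the wait.

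The cost is one date field and some extra analysis. The sensitivity analysis will be less precise: in the middle case above (40 schools, no lag), setting assessments aside could remove the month-12 value for about 38% of controls. The primary randomised comparison is unchanged.

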### Instruments

#### Columbia impairment scale (CIS)

The CIS is a 13-item scale that can be administered by a lay interviewer to either parents or child to provide a global measure of impairment. The 13 items tap four major areas of functioning: interpersonal relations, broad psychopathological domains, functioning in school, and use of leisure time. Items are scored on a spectrum ranging from 0 “no problem” to 4 “a very big problem”. The instrument shows good reliability with Cronbach’s α between 0.70 and 0.89 [28].

#### Children Global Assessment of Functioning (C-GAF)

The Children’s Global Assessment of Functioning (C-GAF) is a practitioner-rated global measure of functioning, which is assessed on a scale from 1 “most impaired” to 100 “superior level of functioning” broken down into 10 equal parts. Shaffer et al. reported an interrater reliability of 0.84 and a test-retest reliability of 0.85 [29].

#### Strengths and Difficulties Questionnaire (SDQ)

The Strengths and Difficulties Questionnaire (SDQ) is a brief behavioural screening questionnaire with 25 items. It exists in a version for youths aged 11–16 years and for parents of 3–16 year olds. The SDQ asks about 25 positive and negative attributes that can be summarized in five subscales: emotional symptoms, conduct problems, hyperactivity/inattention problems, peer relationship problems and prosocial behaviour. Items are scored as “not true”, “somewhat true” and “certainly true” [30].

#### Child behaviour Checklist (CBCL), Teacher Report Form (TRF), and Youth Self-Report Form (YSR)

The CBCL/6–18 consists of 140 items, the TRF of 117 Items and the YSR of 118 Items. Most items are a 3-point likert-scale from 0 (not true (as far as you know)) to 2 (very true or often true). Each form also has different introductory questions that may be rated on a likert scale (with varying numbers of options and anchor points), be open-ended, or multiple-response. The questionnaires can be filled in 10 to 15 min. Subscales that are assessed by summing up items are anxious/depressed, withdrawn/depressed, somatic complaints, social problem, thought problems, attention problems, rule-breaking behaviour, aggressive behaviour. It may also provide information regarding internalizing problems and externalizing problems as well as a total score across all items. The authors of the CBCL report test-retest reliabilities of 0.73–0.94, internal consistency reliabilities (alphas) of 0.63–0.97, and inter-rater reliabilities of 0.57–0.88. For the YSR test-retest reliabilities were 0.67–0.91, and internal consistency reliabilities (alphas) 0.55–0.95. The authors of the TRF report test-retest reliabilities of 0.60–0.96, internal consistency reliabilities (alphas) of 0.72–0.997, and inter-rater reliabilities of 0.20–0.76 [31].

#### KINDL Questionnaire

The KINDL Questionnaire consists of 24 likert-scaled items covering six dimensions: physical well-being, emotional well-being, self-esteem, family, friends and everyday functioning (in school/kindergarten). The six sub-scales can be summed up to a total score. The questionnaire is available as a self report (children/adolescents four to 17 years) and a proxy report version (parents of children between three and 17 years). The scale shows a good reliability (Cronbach’s α > 0.70 for most of the subscales and samples) and a satisfactory validity [32].

### Goals

The main goal of CCSchool, and therefore the primary outcome is to reduce the necessity of inpatient admissions in children and adolescents with mental health and school problems which in consequence may reduce health care costs. In addition, we expect CCSchool to result in increased quality of life as well as social participation in children and adolescents. To achieve these goals early interventions in school will be offered, involving relevant teachers and caregivers into the treatment process. CCSchool comprises the development and evaluation of a model of continuum of care including a collaboration of the mental health system, schools and social services. This model of continuum of care not only results in early treatment by the relevant health professionals of children with mental health problems and impairment in school-participation but also offers intervention in the very place where problems primarily arise: in school.

The implementation of CCSchool requires the establishment of collaboration between the health care and educational systems as well as specific training of therapists via e-learning to use standardized diagnostic procedures and to offer materials for first low-threshold interventions and/or psychoeducation of teachers, parents and children or adolescents.

Secondary outcomes are:Participation in schooling/apprenticeship: Goal: reduction of absenteeism-days from school due; regular school attendanceDisease related specific symptoms: Goal: reduction of mental health symptoms with improvement in level of functioning.Quality of life: Goal: improvement of overall quality of life and in particular in the subscale emotional well-being.Feasibility of CCSchool: establishing (a) a standardized diagnostic procedure for children and adolescents with mental health problems associated with school problems and (b) a school-based treatment in the German Health Care System.

### Evaluation and study analyses

An external independent research institute (IGES Institute GmbH) will evaluate the achievement of the endpoints in CCSchool. The evaluation will use primarily data collected and assessed during the study on level of functioning, level of impairment, absenteeism and quality of life as well as data from documentation and process evaluation. In addition, claims data from the statutory health insurances will be analysed.

The study uses a cluster-randomized design with a waiting-list control group. Participating districts will be randomly assigned to an intervention and a control group. Children and adolescents, who are eligible for participation, will be allocated in the control versus intervention group depending on the location (district) of their school to avoid situations where there are intervention and control participants in the same school/class. The evaluation will compare the resulting intervention and control group participants on all outcome variables. In addition, claims data on the CCSchool participants as well as on children and adolescents with the same inclusion diagnoses (a) living in districts not included in the study and (b) living in the CCSchool districts before CCSchool has started (historical comparisons) will be analysed. These external control participants are matched to the intervention participants by propensity score matching. The claims data allows validating the self-reported data on hospitalization rates and analysing potential effects on health care costs.

The statistical analyses of the comparisons between randomized control group, external control group and intervention group will use a multilevel framework taking the cluster randomisation into account. Longitudinal regression analyses of changes in hospitalization rates, quality of life, symptoms and absenteeism are conducted using mixed models adjusting for potential confounders (e.g., age, gender, regional characteristics). This approach is feasible to estimate within-person changes over time as well as group differences in within-change over time. For process evaluation, cross-sectional group comparisons will be analysed with regression models without repeated measures and descriptive statistics. All effects will be tested with a significance level of *p* ≤ .05.

To minimize selection bias, the study has been presented in each participating region to all child and adolescent psychiatrists and schools. CCSchool teams have invested high efforts in establishing collaborations between hospitals, health professionals in private practice and schools. The outcome variables to be collected are widely used instruments which have been scientifically extensively validated guaranteeing thereby highly standardized and reliable assessments.

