However, in the past decades, continuum of care between the school system, youth welfare system and mental health care services have not been existent in Germany. Reimbursement for psychiatric outreach work was not provided. In the absence of intensive outreach programs, rates of admission to inpatient services among children and adolescents in need of intensive psychiatric treatment were then rather high, while thresholds to use inpatient programs were inadequately lowered, alternative treatment options are lacking [17, 18]. Between 2007 and 2014 inpatient admissions in child and adolescent psychiatry in Germany increased by 38%, while the average duration of stay reduced only by 14%, resulting in an overall increase of inpatient beds needed by 17%. As a consequence transfer of inpatient-treatment effects to school and family surroundings is difficult, diminishing the chances for long-term effects and leading to increasingly often costly and frustrating “revolving door effects” with patients moving back and forth between in- and outpatient settings. On the other hand mental health treatments in natural surroundings (school, family) have been shown to acchieve more stable treatment effects over time. In those settings, relevant problems can be treated where they arise, involving school and family members alike [19–23].

On the 1st of January 2017 the “Act for further development of healthcare and reimbursement of psychiatric and psychosomatic services” (PsychVVG – “Gesetz zur Weiterentwicklung der Versorgung und der Vergütung für psychiatrische und psychosomatische Leistungen”) came into effect in combination with § 115d [24] in Volume V of the German Social Security Code (SGB V). A milestone in provision of care has been laid and the tide has turned: It is now possible for hospitals in Germany to offer continuum of care in form of outreach treatments to patients with mental health issues [25].

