CCSchool will take place in about 20 administrative districts (with an average of 150.000 residents per district), which are evenly randomized into districts for recruitment of the intervention group and districts for recruitment of the control group. Not all health statutory insurances wanted to participate, resulting in about 60% of the children and adolescents in school being eligible for CCSchool. If a child is screened positive and is covered by an health statutory insurance which does not participate in general, the child can enter the contract individually and thereby become eligible for CCSchool.

Assuming hospitalization rates in the eligible population are about five times higher than national average due to the high selectivity (about 5.810 cases per 100.000 children and adolescents), the expected effect of CCSchool treatment will lead to a decline in admissions by 10% (which would then be 5.230 cases per 100.000 children and adolescents). A corresponding power analysis showed that the expected difference can be found when including 20 clusters (districts), with an average cluster-size of 90 patients and a coefficient of variation of k = 2.6 with a power of 90% and an alpha of 5%. Thus, CCSchool plans to recruit about 900 participants in the intervention and control group, respectively, who participate at least in module A. About 50% of subjects are expected to participate in module B and another 30% will be recommended to receive treatment in module C. According to power calculation, a sample of about 900 participants in each group is sufficient to find the expected effects.

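### The before/after claims comparison cannot by itself separate CCSchool from calendar time, and diagnosis-selected external controls may differ in severity, yet both are tested at the same level as the randomised comparison

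*Protocol article*

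**What the plan says.** All of the following is in the protocol article. Under Evaluation and study analyses, districts are randomised and the two randomised groups are compared on every outcome. Claims data are then added for participants and for two external groups with the qualifying diagnoses: (a) children in districts outside the study and (b) children "living in the CCSchool districts before CCSchool has started (historical comparisons) will be analysed". The text continues: "These external control participants are matched to the intervention participants by propensity score matching". The next paragraph puts the randomised control, external control and intervention groups into one multilevel framework. Hospitalisation rates are among the outcomes, age, gender and regional characteristics are given as example covariates, and one significance level of 0.05 covers all effects.

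Three other places bear on this:

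- Background, on trend: "Between 2007 and 2014 inpatient admissions in child and adolescent psychiatry in Germany increased by 38" per cent.
- Background, on the law in force from 1 January 2017: "It is now possible for hospitals in Germany to offer continuum of care in form of outreach treatments".
- Methods/design, on eligibility: a psychiatric diagnosis is needed together with school problems and a C-GAF score of 70 or below.

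Under Goals, inpatient admission is the primary outcome.

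**The concern.** Group (b) lies wholly before CCSchool and the intervention group wholly after its start. In a contrast of their admission rates, period and treatment coincide, so age, gender, region and a propensity score built on such variables cannot pull them apart. Whatever else changed admissions between the two periods is credited to, or charged against, CCSchool.

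Groups (a) and (b) share a second weakness. School problems and C-GAF are ratings made for the study, and claims would not be expected to hold them. Matching cannot balance what is not recorded.

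At stake is how the primary outcome is read. If the randomised and external comparisons disagree on admissions, the article gives no rule for which prevails. Its Discussion links proof of effectiveness to inclusion in regular statutory benefits.

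**Working it through.** **The plan's own effect.** Methods/design gives "about 5.810 cases per 100.000 children and adolescents" without CCSchool and "which would then be 5.230 cases per 100.000 children and adolescents" with it (the dot is a thousands separator). 1 − 5,230/5,810 = 0.0998. This reproduces the stated assumption that "the expected effect of CCSchool treatment will lead to a decline in admissions by 10" per cent.

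**Trend between historical and study periods.** Input: 38% over 2007 to 2014 (Background). Formula: rise over a gap of g years = 1.38^(g/7) − 1.

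- 1 year: 1.38^(1/7) − 1 = 4.7%
- 1.5 years: 1.38^(1.5/7) − 1 = 7.1%
- 2 years: 1.38^(2/7) − 1 = 9.6%
- 3 years: 1.38^(3/7) − 1 = 14.8%

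Counting the span as 8 years gives 4.1% per year, 6.2% at 1.5 years and 8.4% at 2 years.

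The gap is not stated, but a lower limit follows from one assumption. If historical follow-up is as long as study follow-up and ends before CCSchool starts, the midpoints of the two periods differ by at least that length. That is 1 year for a 12-month follow-up and 1.5 years for the 18 months in the Module C section. Recruitment time adds to it.

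Effect on the estimate, if the true reduction is 10%: at 1.5 years the apparent rate ratio is 0.90 × 1.071 = 0.964, a 3.6% reduction. At 2 years it is 0.90 × 1.096 = 0.986, a 1.4% reduction. A rising trend therefore works against CCSchool.

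**The 2017 law.** The article gives a date and no effect size, so nothing can be computed. It matters only if the historical window reaches before January 2017. Ethics approvals date from August and October 2017 and registration from June 2018. If the start lay between October 2017 and June 2018 (assumption), an 18-month look-back begins between April and December 2016 and straddles the law. If outreach lowered later admissions, this would favour CCSchool.

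**Unrecorded eligibility.** Suppose every participant meets the functioning and school criteria, a share p of matched external children does, and meeting them multiplies admission risk by R. With no treatment effect, the ratio of intervention to external rates is R / (1 + p(R − 1)). R and p are assumptions; the article gives neither.

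- R = 2, p = 0.8: 2/1.8 = 1.11
- R = 1.5, p = 0.7: 1.5/1.35 = 1.11
- R = 1.5, p = 0.9: 1.5/1.45 = 1.03

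A ratio above 1 also works against CCSchool.

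**Which group is exposed to what.** Trend and law are national, so a concurrently followed group (a) shares them with the participants. They threaten mainly group (b). The eligibility gap affects both.

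**The case against.** The case on the other side is substantial.

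- **The article signals an order.** The research questions set CCSchool against standard care, the sample size is built on randomised districts, the evaluation rests mainly on data collected in the study, and the stated use of claims is to validate reported admissions and examine costs. External comparisons are never called primary. This stands, but validation needs only participants' own claims, and the analysis paragraph tests all groups at one level.
- **The planned models compare changes within persons.** That removes stable differences in level. With an admission baseline before the index date in both groups, it would also cancel growth at a constant rate, though not an acceleration or a step such as a law. The article describes no such baseline for the external groups, so this protection cannot be counted on.
- **The trend figure is indirect.** It ends in 2014 and counts all admissions, not the rate among diagnosed children. This stands, and is why the sizes are conditional.
- **Matching variables, look-back window and index-date rule may be in the full plan.** Agreed; their absence is not part of this point.

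Some stronger readings are tempting and are not supported. A reader might infer that trend, law and severity each match the 10% effect. Only the trend has a figure in the article, and it comes close only at a gap of about 2 years. A reader might take the assumed admission rate, "about five times higher than national average due to the high selectivity", as the size of the severity bias. That factor includes having a diagnosis, which the external children share. A reader might conclude that the external set cannot be checked against the randomised controls. The three-group comparison already makes that possible. Nor does the point rest on the adequacy of the sample size, which is a separate matter, or on error inflation over several tests, because these comparisons share the intervention arm and a figure for independent tests would overstate it.

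**Conclusion.** The point holds in limited form. A simple contrast of intervention participants with historical children cannot distinguish CCSchool from calendar time. On the article's own trend the distortion is about 7% at a 1.5-year gap and 9.6% at 2 years, against a 10% target. This assumes that growth continued after 2014 and that the diagnosed population followed the national count. The law may add a distortion of unknown size in the opposite direction.

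Both external groups may also be less severely affected than participants. The ratio of 1.03 to 1.11 rests wholly on assumed values. The net direction is unknown and the biases may partly cancel. The external results can therefore support the randomised comparison but should not stand level with it, and the article does not say which is decisive.

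**What to change.** Three changes:

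1. State that intervention versus randomised control is the confirmatory comparison for admissions, and that external and historical results are supportive.
2. Replace the simple historical contrast with a difference-in-differences in claims: the before-to-during change in intervention districts minus the same change in randomised control districts, with non-study districts as a second comparator. Trend and law then cancel as far as they act alike on both sets of districts, which randomisation makes plausible. The same holds for the gap between diagnosis-selected and fully eligible children, if the selection rule is identical in both. Restrict the during period to the first 12 months after recruitment, because the Control group section lets control children enter the intervention afterwards.
3. Report the planned comparison of external with randomised controls as a check on the matching, before any external effect is interpreted.

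The cost is a little more analysis. Claims for participants and for children in the CCSchool districts before the start are already planned. The price is less weight for the external results, and a difference of two changes is less precise than a single before/after contrast.
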